### Ethics Approval

Our study was approved by the institutional review boards of Kyushu University (approval number: 20202021). Written informed consent will be obtained from all participants. Participation will be voluntary, and confidentiality will be maintained. Participants can withdraw from the study for any reason at any time. The intervention will be introduced to the control cluster after the study is completed.

All of the information obtained in our study will remain confidential. Access to information will be limited to the health care workers and data entry management staff for the duration of the study. Research records will be identified only by study ID numbers.

### Dissemination

The results of our study will be disseminated through peer-reviewed journals and international conferences. Additionally, the telehealth care system will be disseminated to other areas in Bangladesh through the collaboration of local communities and research collaborator organizations. Important protocol changes will be communicated to the research ethics committee and the clinical trials registry.

Designing or reporting will not involve patients of the public. However, residents will be involved in interventions, serving as health care workers or local informants. The dissemination plan will be discussed with the local community and research collaborator organizations.

## Results

Recruitment began in June 2020, and it is expected to continue until June 2024. We consented 295 mothers in the study by June 2022. Data cleaning and analysis will begin after the data collection is complete.

## Discussion

In our study, the intervention arm participants are expected to have better health statuses than those of the control arm, as they will receive care through the PHC-MNCH. Our community-based intervention study is extremely important for realizing the continuum of care in MNCH through a telehealth care system and evaluating the improvement of mothers’, newborns’, and children’s health status. Previous studies that investigated the effectiveness of the continuum of care in MNCH mostly focused on the perinatal period [20,21]. Through our trial, we will attempt to show whether the continuum of care, which extends from the antenatal period to the motherhood and childhood periods, is effective in improving the health of mothers and infants. The study will further accumulate evidence on the effectiveness of the continuum of care.

Our proposed study also has a limitation. The intervention sites include some of the areas where we conducted the pilot study. Therefore, some residents of the intervention sites may have a better understanding of the continuum of care than those in the control group. However, since the participants in the pilot study are not included in the proposed study, the effectiveness of the intervention will be evaluated based on its status prior to the pilot study. As such, we believe that this limitation can be controlled.

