## Methods

### Study Design and Sites

Our study is quasi-experimental, and it will be conducted in 6 villages within the Chhaygaon Union of Bhedarganj Upazila (subdistrict), Shariatpur District, Bangladesh (Figure 1; trial registration number: ISRCTN44966621). Located approximately 80 km from Dhaka, these villages are in the suburb of the capital. Among the nine villages in the Chhaygaon Union, the East Chhaygaon, Middle Chhaygaon, and Lakarta villages were purposively set as the intervention cluster, and the Gangshar, Nazimpur, and Aterpara villages were set as the control cluster. The villages were allocated to the intervention and control areas such that the population sizes (intervention area: N=6378; control area: N=6178), geographic locations of the villages, and access to health facilities (each area has a health facility) were similar between the two areas. In the intervention arm, we conducted a pilot study in which we used the PHC system between June 2019 and May 2020 to follow women and infants from 16 gestational weeks to only 6 weeks post partum, with a shorter postpartum follow-up period than the one described herein.

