### Study Population and Selection Criteria

A flow diagram of participants for the enrollment, allocation, follow-up, and analysis stages is presented in Figure 2. Different selection criteria will be applied to intervention, baseline survey, and end line survey participants. The inclusion criteria for intervention participants are (1) women at reproductive age (between 15 and 49 years), (2) women at ≥16 gestational weeks, and (3) women living in intervention villages at the time of enrollment. After birth, their infants will also be enrolled in the intervention cluster.

Baseline survey participants will be women in the intervention and control clusters who experienced giving birth between June 2015 and May 2019 (ie, before the pilot study). End line survey participants will be women in the intervention and control clusters who give birth between November 2020 and October 2024. Women who experience a miscarriage or a stillbirth during this period will also be included as participants.

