### Sample Size

All eligible women and infants at the study sites will be included in our study. Approximately 1000 mother-infant dyads have been deemed eligible for this study among all clusters (500 dyads in each cluster). However, the minimum sample size for recruitment was calculated as 925 dyads for all clusters; 771 dyads in a cluster are required for analyses based on our pilot study, in which the percentage of antenatal care increased by ≥4 times (from 29% to 42%). A 2-tailed test will be conducted (power=0.95; α error=.05). A loss to follow-up rate of 20% was estimated.

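### A pre-pilot baseline and the exclusion of pilot participants do not control pilot carry-over; the antenatal and early postnatal results estimate pilot plus extended programme versus neither

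*Protocol article*

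**What the plan says.** The Discussion raises the limitation itself: because of the pilot, "some residents of the intervention sites may have a better understanding of the continuum of care than those in the control group". It gives two reasons for regarding this as controllable. Pilot participants are left out of the new study, and "the effectiveness of the intervention will be evaluated based on its status prior to the pilot study".

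The dates are in the Methods. Study Design and Sites states: "In the intervention arm, we conducted a pilot study in which we used the PHC system between June 2019 and May 2020". Under Study Population and Selection Criteria, the baseline survey takes "women in the intervention and control clusters who experienced giving birth between June 2015 and May 2019 (ie, before the pilot study"), and the end line survey takes "women in the intervention and control clusters who give birth between November 2020 and October 2024". Recruitment and Consent of Participants opens enrolment to the new programme in June 2020.

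Two sections describe the comparison. Data Collection Methods and Evaluation judges impact by comparing the areas on both surveys. Statistical Analyses names a multilevel logistic regression of the end line survey, adjusted for clustering.

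**The concern.** The limitation is correctly identified, but the stated remedy does not act on it. Moving the reference point back to before the pilot places the whole pilot year inside the interval over which change is measured, and on the intervention side only. Whatever the pilot left behind in the community is then counted in the change.

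Excluding pilot participants removes only their own direct exposure. The route named in the Discussion is better understanding among residents, and neighbours and relatives who were never pilot participants stay in the study.

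What is at stake is attribution. The Abstract's Conclusions and the Discussion look ahead to a statement about the new trial's telehealth programme from the antenatal period through motherhood and childhood. For antenatal and up-to-6-week outcomes, which the pilot already served, the data cannot separate that programme from the pilot. A reader told that the limitation is controlled would assume that they can.

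**Working it through.** No figure in the protocol has to be reproduced here; the point is one of design logic.

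**Step 1. Timeline.**

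| Period | Dates | Where it applies | Section |
|---|---|---|---|
| Baseline births | June 2015 to May 2019 | both areas | Study Population and Selection Criteria |
| Pilot | June 2019 to May 2020 | intervention arm only | Study Design and Sites |
| Recruitment to new programme | from June 2020 | intervention area | Recruitment and Consent of Participants |
| End line births | November 2020 to October 2024 | both areas | Study Population and Selection Criteria |

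The pilot lies wholly between the two survey windows, and the new programme opens the month after it ends.

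**Step 2. What each comparison estimates.** Let c be the lasting pilot gain among intervention-area residents, t the effect of the new programme, s the change over time common to both areas, and d any difference between areas that existed before the pilot.

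- Change from baseline to end line, intervention area: s + c + t.
- Change from baseline to end line, control area: s.
- Difference between these changes: (s + c + t) − s = c + t.
- End line comparison of areas alone: d + c + t.

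Both readings of the analysis keep c. Removing it would need a reference taken after the pilot and before the new programme, and the plan has none.

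**Step 3. Size, as an illustration.** Sample Size reports a pilot rise from 29% to 42%, which I read as the percentage with at least four antenatal visits: 42 − 29 = 13 points. The share that persists is not given, so it is assumed. With t = 0 and d = 0, the spurious gap is that share × 13:

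- 25%: 0.25 × 13 = 3.25 points
- 50%: 0.50 × 13 = 6.5 points
- 100%: 13 points, an extreme bound (see the objection)

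**Step 4. Chance of a significant result, women treated as independent.** Take n = 500 per area (Sample Size), a two-sided 5% test, p1 = 0.29 and p2 = 0.29 + gap. The probability is Φ[(gap − 1.96 × SE0) / SE1], where SE0 = √(2 p̄(1 − p̄)/n) and SE1 = √([p1(1 − p1) + p2(1 − p2)]/n).

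- 25% persisting: p2 = 0.3225, SE0 = 0.02915, SE1 = 0.02913; (0.0325 − 0.0571)/0.0291 = −0.85, giving about 0.20.
- 50% persisting: p2 = 0.355, SE0 = 0.02956, SE1 = 0.02949; (0.065 − 0.0579)/0.0295 = 0.24, giving about 0.60.

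With 400 per area (500 less 20% loss) these become 0.17 and 0.50. A baseline-adjusted comparison of four cells of 500 gives about 0.12 and 0.35. All of these overstate the chance of P<.05 under the planned model, which adjusts for clustering with three villages per arm. They are not estimates of the trial's error rate.

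**The case against.** **The target may be the telehealth system as a whole.** The Abstract's Objective and the end of the Introduction ask whether the telehealth system works; neither claims an increment over the pilot. For that question a pre-pilot baseline is the fitting choice, since a baseline already raised by the pilot would understate the effect. This stands, and it is why the baseline itself should not change. But under that target the carry-over is part of the effect, not a limitation to be controlled. The Discussion treats it as a limitation, and no section defines a combined effect.

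**The effect of carry-over is easily overdrawn.** A reader might infer that the whole 13-point rise could persist and produce an almost certain positive result for a programme that adds nothing. The documents do not support this. Study Outcomes and Measurements counts checkups delivered with the Portable Health Clinic as care visits, and the new programme schedules four antenatal ones. It would add nothing to uptake only if those visits were missed or merely replaced facility visits. If the pilot's 42% also counted its own delivered visits, which Sample Size does not say, that part of the rise would stop when the visits stopped.

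**A first-birth subset does not solve it.** Restricting to women whose first birth falls in the end line window mainly removes a woman's own pilot exposure, not learning from neighbours. Nor does it guarantee that there was no pilot pregnancy. An earlier pilot pregnancy may have ended in miscarriage. A woman at 16 weeks in late May 2020 would, with a 40-week pregnancy, deliver 24 weeks later, about mid-November 2020, inside the end line window.

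**The limitation is disclosed and the wording is hedged.** True, and this keeps the point to interpretation. But the conclusion drawn from the disclosure is still wrong, and an analysis plan that is not shown could not make the stated argument valid.

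**Conclusion.** The point holds in a limited form. Neither excluding pilot participants nor using a pre-pilot reference controls the carry-over that the Discussion describes. Judged from the pre-pilot baseline, the antenatal and up-to-6-week results estimate lasting pilot gain plus new programme effect; the end line model keeps the pilot gain as well. This rests only on the stated dates and on the pilot having run in the intervention arm alone.

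The size is not known, nor is it known whether any gain lasted. Persistence of 25% or 50%, both assumed, would give a spurious gap of about 3 or 6.5 points.

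The documents do not show that the baseline is wrongly chosen, that the survey comparison is unusable, or that a false-positive result is likely. Outcomes after 6 weeks lie beyond the pilot's follow-up and are less exposed, but pilot education could still influence them.

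**What to change.** 1. In the Discussion, delete the closing statement that the limitation can be controlled.
2. State that the antenatal and up-to-6-week results estimate the combined effect of the 2019-2020 pilot and the extended programme versus neither. Word the Abstract's Conclusions and the Discussion's own conclusions to match.
3. Describe outcomes after 6 weeks, such as complementary feeding at 6 months, as less exposed to carry-over, not free of it.
4. Optionally, show a first-birth subset as an exploratory analysis, labelled as mainly removing a woman's own pilot exposure.

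Items 1 to 3 cost only wording; the downside is a less specific headline claim. Item 4 would use survey data and need no extra participants or visits, but its estimate would be less precise. The Results section places data cleaning and analysis after data collection is complete, so the change can be made before any analysis.

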## Appendix

Multimedia Appendix 1 Device specifications.

Multimedia Appendix 2 Health education content.

Multimedia Appendix 3 Excerpts of criteria for antenatal checkup.

Multimedia Appendix 4 Participant timeline of the Portable Health Clinic for Maternal, Newborn, and Child Health intervention study.

## Abbreviations

MNCH: maternal, newborn, and child health
PHC: Portable Health Clinic
PHC-MNCH: Portable Health Clinic for Maternal, Newborn, and Child Health
